## Abstract

**Background:**

Students following a low education track have an increased risk for developing problem behaviors. Rock and Water is a widespread, but still poorly evaluated, intervention that aims to improve students’ socio-emotional adjustment and social safety. The aims of this study are to evaluate (1) the effectiveness of Rock and Water on socio-emotional adjustment (i.e., psychosocial wellbeing, sexual autonomy, and resilience) and social safety (i.e., perceived social security in the classroom, aggression, and bullying) and to examine (2) moderators and (3) mediators of its effects.

**Methods:**

Schools are randomly assigned into four conditions: ‘Light’ (a core team of teachers is trained), ‘Standard’ (a core team of teachers and the whole school team is trained), ‘Plus’ (a core team of teachers, the whole school team is trained, and parents are involved), or ‘Control condition’ (Care As Usual). We aim to include 180 7th Grade students in each condition (*N* = 720) across all waves. A multi-informant (i.e., students, parents, and teachers) approach is used to assess the outcomes (socio-emotional adjustment and social safety), moderators (student, trainer, and parent characteristics) and mediators (self-control, self-reflection, self-esteem, and emotion regulation). Video-observations will be analyzed in a subsample to study the possible mediating effect of changes in deviant and prosocial communication among students on the effect on social safety.

**Discussion:**

This project will provide information on the effectiveness of (different levels of school and parental involvement in) Rock and Water, which can be used by schools to decide upon the most efficient way to improve the care for the students. We will be able to shed more light on what works for whom and the working mechanisms of Rock and Water.

**Trial registration:**

Dutch Trial Registration number 6554, registered on the 3rd of July 2017. The design of this study was approved by the Ethical Committee of the Faculty of Social and Behavioral Sciences of Utrecht University (FETC17–015). This study is financially supported by a grant from The Netherlands Organization for Health Research and Development, grant number 531001106.

**Electronic supplementary material:**

The online version of this article (10.1186/s40359-018-0247-y) contains supplementary material, which is available to authorized users.

## Background

In the Netherlands, secondary education (starting at age 12) consists of three education tracks: Preparatory vocational education track, preparatory college track, and preparatory university track. These different education tracks are attended by respectively 43, 28, and 29% of the total student population of secondary education [1]. Students following the preparatory vocational education track (prevocational students) show less autonomy, less academic performance, and less school motivation and commitment than students in the other two tracks [2]. They have an increased risk for psychological problems, such as substance abuse and early sexual intercourse [3, 4], compared to students following the other two tracks. For instance, of the prevocational students about 17% smokes, 48% binge-drinks, and 25% has sex under the age of 17, whereas of students following the preparatory college or university track respectively 5 and 2% smokes, 37 and 25% binge-drinks, and 12 and 6% has sex under the age of 17 [4]. Due to the high level of problems prevocational students might encounter, it is important to positively stimulate their development. Nowadays schools often implement various programs to obtain such aims, especially since the government requires schools to execute a policy to improve students’ socio-emotional adjustment and social safety within the schools.

Rock and Water (R&W) [5, 6] is one of such programs. It is a universal school-based intervention that aims to improve students’ socio-emotional adjustment and social safety by increasing their self-control, self-reflection, self-esteem, emotion regulation and communication skills. R&W uses a psychophysical approach, that is play and exercises are used to increase the strength of youth, to teach them to make (physical) contact with others and to explore, respect and set own and other’s boundaries. The name of the intervention is based on the symbolic principles of ‘rock’ and ‘water’. Rock indicates a rigid and uncompromising attitude: Sticking to your own opinion and not bending for the opinion of others. Water on the other hand represents flexibility and cooperation: Being aware of one’s own opinion, thoughts and feelings and being open to those of others at the same time, willing to cooperate with them. R&W addresses multiple themes including relaxation, self-control, physical and verbal communication, body language, assertiveness, group pressure, sexuality, and sexual violence.

Especially the psychophysical approach makes R&W eminently suitable for prevocational students. These students are less intrinsically motivated for school and (verbal) learning than students of other education tracks [2] and their cognitive abilities are, generally, lower [7]. Learning through play and exercise increases their motivation and is cognitively less demanding than a verbal cognitive approach. Hence, R&W fits in well with the learning style of prevocational students.

R&W is implemented in many countries (e.g., Australia, China, Singapore, France, The Netherlands). Despite this broad implementation, little information about the effectiveness of this intervention is available. Results of several small-scaled studies showed that participants feel more resilient, experience a more positive identity and use more active than passive coping styles after completing R&W [8]. Additionally, a recent study found that boys’ self-reported coercive strategies and verbal manipulation decreased and their self-regulation and general efficacy increased after following the intervention [9].

Notwithstanding these promising results, these studies have several limitations. First, most studies included boys only. It is unknown what the effects are for girls, for youth with different ethnic backgrounds and for prevocational students in specific. Second, only two measurement points were used, prior to the intervention and immediately after the intervention. Changes during the intervention as well as the long-term effects of R&W were not examined. Third, outcomes were narrowly defined [8] which makes it unclear what the effects are on the broader concept of socio-emotional adjustment and social safety. Fourth, often only one informant, mostly the adolescents themselves, participated and only one type of data collection was used, mostly questionnaires. Lastly, the studies did not examine potential moderators or mediators. Hence, no information is available about differential effectiveness for certain subgroups and the working mechanisms of R&W.

To increase the knowledge about the effectiveness and working mechanisms of R&W we will conduct a Randomized Controlled Trial (RCT) in which we plan to overcome the above mentioned limitations. We aim to include prevocational boys and girls from different ethnic backgrounds, conduct measurements prior, during, immediately after R&W and six months later, assess a broad range of outcomes (i.e., socio-emotional adjustment and social safety), use students, parents, and teachers as informants, utilize questionnaires, a computer task, and video-observations, and study potential moderators and mediators.

The first aim of the RCT is to examine the effectiveness of R&W in improving students’ socio-emotional adjustment (i.e., psychosocial wellbeing, sexual autonomy, and resilience) and social safety (i.e., perceived social security in the classroom, aggression, and bullying). We will study R&W in three different conditions and compare it to a control group receiving Care As Usual (CAU; i.e., current school policy to enhance socio-emotional adjustment and social safety of students). We hypothesize that R&W will improve students’ socio-emotional adjustment and social safety and will outperform CAU. The experimental conditions differ in the number of parties that are involved in R&W, that is a core team of teachers, a core team of teachers and the whole school team, and a core team of teachers, the whole school team and parents. The more parties are involved, the broader the ecological focus of the intervention will be. According to the social ecological model of Bronfenbrenner [10] behavior is determined by the interaction of multiple systems (i.e., the individual, family, school). The involvement of multiple systems in the intervention could increase the effectiveness of R&W. Although, this positive effect of involvement of multiple systems is not always found [11]. We will examine if R&W is more effective the more parties are involved, as suggested by Durlak and colleagues [11]. We hypothesize that students’ improvements will be more evident the more parties are involved.

The second aim is to examine potential moderators of the effect of R&W. Several student characteristics will be examined as moderators: Gender, ethnicity, and personality. In the R&W program the emphasis is on physical exercises which might lead to differential effectiveness based on gender and ethnicity. There are differences in the levels of daily physical activity between boys and girls with girls being less physically active [12, 13]. Girls appear to experience higher barriers for physical activities than boys. They are more afraid of being chosen last for a team and of being embarrassed [13]. Therefore, we hypothesize that R&W is more effective for boys.

Also between ethnicities there are differences in the amount and sort of physical activities adolescents engage in. For instance, Black and Asian adolescents are less physically active and show more sedentary behavior than White adolescents [12, 14]. White girls are more likely to be active in sports teams than Hispanic girls whom are more likely to be active in walking for transportation or physical activities at home such as household chores [15]. Kelly and colleagues [15] suggest to tailor physical activity programs based on ethnicity due to differences in factors related to physical activation. For example, White girls appear to have higher levels of self-efficacy related to physical activities which makes them more physically active than Black and Hispanic girls. It might be that White students are more familiar with the sort of physical exercises used in the R&W program than students with other ethnicities. These White students might be less out of their comfort zone due to which they can focus more on the other aspects of the intervention. Thus, we hypothesize that R&W is more effective for White students than for students with other ethnicities.

Previous intervention research has shown that personality can be a moderator of intervention effectiveness. Senf and Liau [16] have found the strongest intervention effects on happiness for individuals with high levels of extraversion and openness and on depressive symptoms for individuals with high levels of extraversion. Asscher and colleagues [17] have shown that Multisystemic Therapy was less effective than treatment as usual in decreasing rule-breaking behavior for adolescent with low levels of agreeableness. Stoltz and colleagues [18] have found the strongest intervention effects on reactive aggression for children with a low level of extraversion and on proactive aggression for children with less extreme levels of conscientiousness. Hence, it is expected that personality also influences the effectiveness of R&W. It is hypothesized that R&W is most effective for students with higher levels of agreeableness and openness, and average levels of conscientiousness. No specific hypothesis concerning extraversion is stated, since the results [16, 18] are inconsistent.

Besides the student characteristics, we will also study trainer characteristics: Gender, ethnicity, education level, level of self-perceived competence, expertise, and degree of training and supervision. Findings concerning characteristics of professional therapists are inconsistent. Whereas some studies have found significant impact of (one of) these characteristics on treatment outcome [19–21], other studies have found no relation [22, 23]. Characteristics of (non-professional) therapists are often neglected in intervention studies. By studying trainer characteristics of non-professional therapists as moderators we will clarify the role of these characteristics on the effectiveness of R&W. We hypothesize that R&W is more effective when trainers are males, have a Western ethnic background, have a higher education level, have more self-perceived competence, have more expertise, and received more training and supervision.

Additionally, we will analyze parental characteristics as moderators: Parental sense of parenting competence and positive parenting (i.e., parental warmth and monitoring). Parents with a high sense of competence feel capable and adequate in interactions with their child [24]. It might be that due to this confidence parents are more susceptible for information about the strategies and ‘language’ of R&W and apply these at home. Positive parenting enhances adolescents’ social competence [25] and the parent-child relationship [26]. It might be that these adolescents feel more competent to incorporate R&W into their daily lives and tell their parents about R&W within that close and trusting relationship. Parents learn more about this intervention which enables them to also apply R&W. Therefore, we hypothesize that R&W is more effective for students with parents with high levels of parental sense of competence and positive parenting.

The third aim is to study the working mechanisms of R&W. Self-control, self-reflection, and self-esteem will be examined as mediators of the effect of R&W on students’ socio-emotional adjustment and social safety. Self-control, self-reflection, and self-esteem are theorized as the three pillars through which R&W aims to establish the desired developments [5]. Additionally, emotion regulation will be examined as mediator. According to the theory behind R&W, students will become better aware of the physical representations of their emotions, for instance muscle tensions and a-rhythmic breathing. Raising students’ emotional awareness is expected to facilitate them to perceive their emotions and regulate them. This improvement in emotion regulation would lead to an increase in their socio-emotional adjustment and social safety [5]. Analyzing these mediators enables us to test the theory of R&W. We hypothesize that R&W will increase students’ self-control, self-reflection, self-esteem, and emotion regulation which, in turn, will enhance their socio-emotional adjustment and social safety.

Furthermore, deviant and prosocial communication (i.e., verbal and non-verbal) will be analyzed as mediators of the effect of R&W on social safety. Communication is a recurrent theme throughout the intervention. It is proposed in the theory that improving the communication of students increases their feelings of social safety, as they learn to show that they care about someone’s feelings, that they are open to others and can become closer to each other [5]. Therefore, we hypothesize that R&W decreases deviant communication and increases prosocial communication which improves students’ social safety.

In sum, in this study we will examine the effectiveness of R&W in improving students’ socio-emotional adjustment and social safety. Moreover, we will examine what works for whom by studying characteristics of students, teachers and parents. Additionally, the working mechanisms of the intervention will be analyzed.

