The R&W program is implemented in the schools for two years. The program starts in 7th Grade with 14 weekly lessons of one and a half hour. In 8th Grade students receive 8 weekly lessons of one and a half hour (see Table 1 for an overview of the topics per lesson). The lessons are given to the class as a whole in large spaces such as a gym hall or drama classroom. The trainers are (mostly) physical education teachers of the schools whom have participated in the three-day training course provided by the Gadaku Institute. These trained and certified teachers are monitored and supervised during the study by coaches of the Gadaku Institute. These coaches have at least once a week contact with the R&W trainers in the schools by e-mail, telephone, or face-to-face depending on the needs of the trainers. They answer questions and give advice regarding the R&W program. Additionally, the coaches observe a lesson of the trainer and provide feedback based on that observation.

**Table 1 Tab1:** Overview of the Topics of the R&W Lessons in Year 1 and in Year 2

Year 1 (7th Grade)		Year 2 (8th Grade)	
Lesson	Topic	Lesson	Topic
1	Standing strong (Relaxation)	1	Refresh skills year 1
2	Standing strong together (Helping each other in confrontation)	2	Breathing (Relaxation)
3	Physical and mental pressure	3	Body language
4	Bullying (Ignoring)	4	Peer pressure and bullying
5	Bullying (Walking away)	5	Peer pressure (Sexual autonomy)
6	Verbal communication	6	Responsibility and making own choices
7	R&W in school	7	Sexual autonomy (Boundaries)
8	Breathing (Relaxation)	8	Positive thinking and visualization
9	Body language		
10	Personal contact		
11	Experiencing, respecting, and setting boundaries		
12	Experiencing, respecting, and setting boundaries		
13	Intuition		
14	Dealing with intimidating group		

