#### Moderators

Students’ gender and ethnicity and trainers’ gender, ethnicity, education, expertise, and degree of received training and supervision are assessed with questionnaires developed for this study.

Students’ personality is reported by the student and parent using the Quick Big Five [41]. It consists of 30 items (i.e., characteristics; e.g., nice, sympathetic, organized) on which the informant can indicate to what extent that characteristic suites the participant.

Parental sense of parenting competence is assessed with the subscale Competence of the Parenting Stress Index [42] completed by the parent. It measures the degree to which parents feel they are capable enough and have enough skills to cope with their child. The subscale contains 8 items (e.g., “Raising my child is harder than I expected.”).

Positive parenting will be measured using the subscales Warmth and Monitoring from the Co-parenting Behavior Questionnaire [43] completed by the parent. The subscale Warmth (7 items; e.g., “I spend time doing fun things with my child.”). measures the extent to which parents show parenting behavior to make their children feel comfortable, accepted and approved. The subscale Monitoring (5 items; e.g., “I know my child’s after school activities.”) measures parental awareness of different aspects of the children’s life.

Teacher’s sense of competence will be assessed with the subscale Self-efficacy for management of the Teachers’ sense of self-efficacy [44] completed by the R&W trainer. This subscale measures teachers’ confidence in their skills to effectively manage their classroom. It contains 6 items (e.g., “How much can you do to control disruptive behavior in the classroom?”).

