#### Statistical analyses

The power calculations are based on the N:q rule for structural equation models [59]. This rule states that for each free parameter (q) 10 to 20 participants (N) are needed. We took the conservative approach by taking 20 participants per free parameter for our power calculations. In our multigroup LGC model there are 9 free parameters per condition, 36 free parameters in total. Thus a total sample of 720 participants is needed for our analysis, 180 participants in each condition. Since not only students can drop out but also classes (about 20 students) and schools (about 60 to 90 students), we will include three to four schools per condition. Missing data will be handled in M*plus*.

In our data, students are nested in classes which are nested in schools. Therefore, we will examine whether there is significant intra-class correlation on one of the levels (i.e., school, and class) and we will calculate the design effect. Each level with a design effect larger than 2.0 will be modeled in the analyses which allows us to correct for the nested data, that is multilevel analyses [60].

The first aim is to examine the effectiveness of R&W in the conditions which differ in the number of parties involved in the intervention. This will be examined using an analysis of covariance (ANCOVA) for the outcomes of socio-emotional adjustment and social safety, in case the design effect is smaller than 2.0. The dependent variables will be the post-measurements after the second year (8th Grade), the independent variables the condition, and the covariates the premeasurements (7th Grade). If needed, due to large design effects, multilevel regression analyses will be used (This also holds for the other aims). Then, we will analyze the trajectories of change in socio-emotional adjustment and social safety during R&W with multigroup Latent Growth Curve (LGC) modeling in M*plus*. We will examine if these trajectories of change differ significantly between the four conditions.

The second aim, the effect of potential moderators on the effectiveness of R&W on socio-emotional adjustment and social safety, will be examined using ANCOVAs for categorical moderators and regression analyses for the continuous moderators. The interaction effects of the concerned outcome measure with the student, trainer or parent characteristics will be added as an interaction term.

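### Trainer characteristics cannot be tested as moderators of the R&W effect against CAU, because R&W trainers exist only in the R&W conditions; the trainer analyses should be re-labelled as exploratory and within R&W

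*Protocol article*

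**What the plan says.** All references are to the protocol article.

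- **Aim (Background).** "The second aim is to examine potential moderators of the effect of R&W". The effect itself is set against usual care under the first aim: "We will study R&W in three different conditions and compare it to a control group receiving Care As Usual".
- **Trainer moderators (Background).** "we will also study trainer characteristics: Gender, ethnicity, education level, level of self-perceived competence, expertise, and degree of training and supervision". The hypotheses are directional: R&W is expected to work better with male, Western and more highly educated trainers, and with those who "have more self-perceived competence, have more expertise, and received more training and supervision". The stated purpose is: "By studying trainer characteristics of non-professional therapists as moderators we will clarify the role of these characteristics on the effectiveness of R&W".
- **Measurement (Moderators).** Trainer gender, ethnicity, education, expertise, and training and supervision received come from study questionnaires. Sense of competence is "completed by the R&W trainer". No counterpart in control schools is described.
- **Who the trainers are (Design; Rock and water; Control condition).** They are mostly physical education teachers certified through the three-day R&W course, which belongs to the R&W conditions. Control schools continue existing policy, which in some schools is only a management-level measure.
- **Supervision (Rock and water).** Coaches are in touch with trainers at least weekly, "by e-mail, telephone, or face-to-face depending on the needs of the trainers".
- **Analysis (Statistical analyses).** ANCOVA for categorical moderators and regression for continuous ones; "student, trainer or parent characteristics will be added as an interaction term". The text does not limit the trainer analysis to the R&W arms. It also pairs the characteristic with the outcome measure, not with condition.

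**The concern.** Moderation of the R&W effect means that the difference between R&W and CAU changes with the moderator. Estimating it needs the moderator in both groups. Student and parent characteristics meet that condition, since they exist in all four conditions. Trainer characteristics do not.

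Within R&W, the slope of outcome on a trainer trait mixes two things: any change in the programme's effect, and any relation of the trait to outcome that would exist without the programme. The trainers are mostly the schools' own teachers. Their gender, education or classroom management may follow the school's intake, or affect students directly. Without a control counterpart the two cannot be separated.

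At stake is a statement that R&W works better with certain kinds of trainer, made without a comparator and resting on few trainers. For supervision there is a further problem: the amount received arises after randomisation and is not assigned, so trainers in difficulty may receive more.

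**Working it through.** **The plan's own figures.** 9 free parameters x 4 conditions = 36; 36 x 20 = 720; 720 / 4 = 180 per condition. These reproduce and are not in dispute. The three R&W conditions hold 3 x 180 = 540 students. At three to four schools per condition, that is 9 to 12 R&W schools and 3 to 4 control schools.

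**Is the interaction identified?** Let T = 1 for R&W and 0 for CAU, and let M be the trainer trait:

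Y = b0 + b1 T + b2 M + b3 T·M

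- Control coded as any constant c: T·M = M − c + c·T, an exact combination of the other columns. Rank is 3 of 4.
- Control dropped because M is missing: T is 1 throughout and T·M = M. Rank is 2 of 4.
- Four-arm version (three condition indicators, M, three products): rank is 7 of 8.
- R&W arms only (Light/Standard/Plus, M and products): rank is 6 of 6.

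The ranks are the same with 3 or 4 schools per condition. Within R&W the slope on M is b2 + b3. It equals the moderation effect b3 only if b2 = 0, which these data cannot check.

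**How much information is there?** The documents give no number of trainers. If each school had one trainer value, with two-sided alpha 0.05 and 80% power (all assumptions), the smallest detectable school-level correlation by Fisher's z is tanh[(1.960 + 0.842) / √(n − 3)]:

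- n = 9: tanh(2.802 / 2.449) = 0.82
- n = 12: tanh(2.802 / 3) = 0.73

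Each school trains a core team, so trainers may outnumber schools. One per class of about 20 would give 540 / 20 = 27, still far fewer than 540.

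**Clustering under the plan's rule.** A level is modelled only if its design effect exceeds 2.0. For a trait constant within cluster, design effect = 1 + (m − 1) x ICC, and the type I error when clustering is ignored is 2[1 − Φ(1.96 / √design effect)]. The documents give no ICC; 0.016 is assumed.

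| Case | Design effect | Modelled? | Type I error if ignored |
|---|---|---|---|
| School of 60, ICC 0.016 | 1 + 59 x 0.016 = 1.94 | No | 16.0% |
| At the cut-off | 2.00 | No | 16.6% |
| School of 90, ICC 0.016 | 1 + 89 x 0.016 = 2.42 | Yes | not applicable |
| Trait varies by class of 20, ICC 0.016 | 1 + 19 x 0.016 = 1.30 | No | about 9% |

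**Supervision.** Illustration with assumed values: need has a standardised effect of −0.3 on outcome, and supervision has no true effect. A need-supervision correlation of 0.3, 0.5 or 0.7 then gives a spurious supervision slope of −0.3 x 0.3 = −0.09, −0.3 x 0.5 = −0.15 or −0.3 x 0.7 = −0.21. All three run against the hypothesised direction. The documents give no value for any of these quantities.

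**The case against.** The strongest reply is that the article never says control students enter the trainer analysis. Competence is taken from the R&W trainer, and the aim is motivated by studies of therapist characteristics and treatment outcome, which suits an analysis within R&W. That model is estimable, and which arms enter a model is often settled in an analysis plan. This stands as far as it goes: a reader might infer that no trainer analysis is possible, and that would be wrong. It does not rescue the stated aim. The article itself fixes the effect to be moderated and the directional hypotheses, and an analysis plan cannot supply control-arm trainer data that are not collected.

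Several stronger readings are not supported:

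- **A 32% type I error.** An ICC of 0.05 with 60 students per school gives a design effect of 1 + 59 x 0.05 = 3.95, and 32% if clustering is ignored. The plan would model that level, and it says the multilevel rule holds for the other aims too.
- **Exactly 9 to 12 units.** That counts schools. Core teams may supply several trainers each, and traits may differ between classes.
- **Almost no degrees of freedom with six traits.** Nothing says the traits enter one model together.
- **Supervision known to follow need.** The phrase about needs may describe only the mode of contact, and every trainer has the weekly minimum. What stands is that the amount above that minimum is not assigned.
- **Control schools stated to have no R&W trainer.** This is inferred. Study sample excludes only whole-school use of R&W, so an isolated trainer in a control school is conceivable, but that person would not deliver the trial programme.

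The reach is also limited. This is one part of the second aim, the first aim is untouched, and the Discussion links possible programme adjustments to student characteristics.

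**Conclusion.** The point holds in a limited form. Trainer characteristics, as measured, cannot be tested as moderators of the effect of R&W against CAU. This rests on the inference that control schools have no R&W trainer and on the measures being planned for trainers only. Associations within R&W, and differences between Light, Standard and Plus by trainer trait, can be estimated, but they are non-randomised with respect to the trait and do not show greater effectiveness with certain trainers.

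The trainer-level information is much smaller than 540 students suggests. A type I error of up to about 16-17% applies only if a trait is constant within school, the design effect is just below 2.0 and clustering is then left out; it is lower for class-level variation at the same assumed ICC. Confounding of supervision by need is a well-founded risk of unknown size, not an established bias.

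**What to change.** 1. In Background (second aim) and Statistical analyses, describe the trainer analyses as exploratory predictors of outcome within the three R&W conditions, and drop the wording that they show for which trainers R&W is more effective.
2. Fit them in those conditions only, adjusted for condition and the baseline measure. Model trainer/school clustering whatever the design effect, use small-sample degrees of freedom, and report estimates with intervals.
3. Report degree of training and supervision as an implementation measure, or keep it with an explicit caveat on confounding by need.
4. Keep the moderator tests for student and parent characteristics, and word the interaction term as condition by characteristic.

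The cost is a change of wording and no new data. The trainer hypotheses become exploratory, and their intervals will be wider.
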